**Methods/design:**

A cluster randomized controlled trial will be conducted in 16 eligible districts (clusters) in the Eastern Region of Ghana to assess the effect of an mHealth CDMSS for maternal and neonatal health care services on maternal and neonatal outcomes. The CDMSS intervention consists of an Unstructured Supplementary Service Data (USSD)-based text messaging of standard emergency obstetric and neonatal protocols to providers on their request. The primary outcome of the intervention is the incidence of institutional neonatal mortality. Outcomes will be assessed through an analysis of data on maternal and neonatal morbidity and mortality extracted from the District Health Information Management System-2 (DHIMS-2) and health facility-based records. The quality of maternal and neonatal health care will be assessed in two purposively selected clusters from each study arm.

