### Sampling of clusters for quality of care study

One well-resourced and one poorly resourced cluster will be purposively selected from each study arm. The selection criteria will be based on the number and mix of health facilities in the district and the midwife to number of deliveries (per annum) ratio in a district. While purposive selection of these study districts does not allow generalizability of findings, application of these qualitative methods provides insight into how and why the intervention worked or not.

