The QOC of neonatal and maternal health care services will be assessed by measuring health provider adherence to the standard emergency protocols at baseline and at the end of the study. Provider adherence to these protocols for common neonatal and maternal conditions will be assessed using a checklist based on the SMP in use in Ghana. Qualitative assessment (focus group discussions and key informant interviews among health care workers) as to how the intervention was used and why it produced the effects observed will be conducted in the two intervention districts where the QOC study will be conducted.

All data will be collected in an anonymous format. Double entry of data collected will be done and data will be handled in accordance with Good Clinical Practice. Figure 3 summarizes the schedule of enrollment and time points for assessments for this study.

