## Outcome measures

Institutional neonatal mortality will be considered as the primary outcome measure for this study. For this study neonatal mortality is defined as death of a newborn occurring from birth up to the 28th day of life [12]. Multiple secondary outcome measures pertaining to maternal and neonatal outcomes will also be measured. Aggregate data on primary and secondary outcomes will be extracted from (DHIMS-2) and health facility health record books for non-hospital facilities (Table 1).

**Table 1 Tab1:** Data sources for outcome measures

Outcome measure	Source of data			
	Hospital	Health centre	CHPS	Maternity home
Number of cases of birth asphyxia	DHIMS-2	Facility	Facility	Facility
Number of cases of low birthweight	DHIMS-2	Facility	Facility	Facility
Number of cases of neonatal jaundice	DHIMS-2	Facility	Facility	Facility
Number of cases of neonatal sepsis^a^	DHIMS-2	Facility	Facility	Facility
Number of cases of PIH/pre-eclampsia/eclampsia	DHIMS-2	Facility	Facility	Facility
Number of cases of postpartum hemorrhage	DHIMS-2	Facility	Facility	Facility
Number of cases of prolonged labor	DHIMS-2	Facility	Facility	Facility
Number of cases of puerperal sepsis	DHIMS-2	Facility	Facility	Facility
Number of cases of neonatal deaths	DHIMS-2	Facility	Facility	Facility
Number of cases of maternal deaths	DHIMS-2	DHIMS-2	DHIMS-2	DHIMS-2
Total number of deliveries	DHIMS-2	DHIMS-2	DHIMS-2	DHIMS-2
Total number of ANC attendants	DHIMS-2	DHIMS-2	DHIMS-2	DHIMS-2

^a^Cord sepsis used as a proxy for neonatal sepsis in this study; *ANC* antenatal clinic, *CHPS* Community-based Health Planning and Services, *DHIMS-2* District Health Information Management System-2, *PIH* pregnancy-induced hypertension

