Descriptive analysis of the adherence of health care providers to standard maternal and neonatal protocols will be done by cluster. Logistic regression will be applied to investigate the association between health provider adherence to protocols and the incidence of maternal and neonatal mortality. Responses from focus group discussions and key informant interviews will be manually transcribed, analyzed and grouped into various themes emphasizing the key convergent and divergent views that explain how and why the health care providers adhered, or did not adhere, to the intervention protocols.

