Though this study will provide much needed evidence to bridge the knowledge gap about the effect of mHealth intervention on maternal and neonatal health outcomes, the study has some limitations. Firstly, we assume that once the USSD platform is assessed, the information retrieved will be used for action; this may not always be the case. We expect that the assessment of the QOC of maternal and neonatal health care services in the four purposively selected clusters will address this limitation to a large extent. Secondly, there is generally a limitation with regard to network availability, electricity and well-functioning phones in Ghana, particularly in the rural areas; this may affect the ability of health care providers in some remote areas to use the intervention. Thirdly, this study will not assess neonatal or maternal mortality at the community level. The attributable risk of death for neonates born at home compared to those born in health facilities in SSA is estimated to be 21% [53]. The DHIMS-2 database from which data for evaluation of the CRCT will be extracted is a web-based platform built on the District Health Information System-2 (DHIMS-2) open source software. DHIMS-2 serves as a data recording, collection, collation and analysis tool that hosts the entire national health data of Ghana. Data entry into the DHIMS-2 is done using primary data collection tools and standard registers designed for various health services and programs. The DHIMS-2 does not capture community-level health outcomes. The contribution of out-of-facility deaths to maternal and neonatal mortality is, therefore, not captured in the DHIMS-2. The CDMSS has also been implemented as an institutional-based support system to be used by health facilities that contribute data to the DHIMS-2. Thus, community-level data (contribution of the out-of-health facility deliveries to neonatal and maternal deaths) will not be assessed in this study. However, given that 74% of deliveries in Ghana occur in a health facility with a skilled attendant [27], we expect our sample to include the majority of maternal and neonatal clients because clients who self-select to deliver at health facilities are usually followed up in the communities by the health workers. These clients are likely to seek health care services from these facilities. Lastly, there may be concurrent maternal and neonatal health care interventions running at the time of the trial. These interventions could influence the results of our study although they are likely to be independent from the randomization. However, the study team will document all concurrent maternal and neonatal health services occurring in the study sites and carefully interpret our results based on this real-life context.

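### The planned logistic regression of mortality on provider adherence rests on four purposively chosen districts with no provision for clustering, so its standard inference would be unreliable

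*Protocol article*

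**What the plan says.** Adherence is the sub-study's measure of quality of care. Under Data collection: "The QOC of neonatal and maternal health care services will be assessed by measuring health provider adherence to the standard emergency protocols", by checklist, at baseline and at the end. The Abstract limits where this happens: "The quality of maternal and neonatal health care will be assessed in two purposively selected clusters from each study arm". The section on sampling of clusters for the quality of care study gives the rule, "One well-resourced and one poorly resourced cluster will be purposively selected from each study arm", and the Discussion confirms the count by referring to "the assessment of the QOC of maternal and neonatal health care services in the four purposively selected clusters".

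The Statistical analysis section then plans two things. The first is descriptive: "Descriptive analysis of the adherence of health care providers to standard maternal and neonatal protocols will be done by cluster". The second is inferential: "Logistic regression will be applied to investigate the association between health provider adherence to protocols and the incidence of maternal and neonatal mortality". The second sentence gives no level at which adherence enters, no covariates and no treatment of clustering. The preceding paragraph does provide for clustering and confounders, but for the logistic models of the decision-support system's effect on the outcomes.

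The sampling section concedes one limit: "While purposive selection of these study districts does not allow generalizability of findings". On the outcome side, the Outcome measures section begins "Aggregate data on primary and secondary outcomes will be extracted from (DHIMS-2" and adds facility record books for non-hospital sites.

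**The concern.** A logistic regression treats births as independent unless told otherwise. Here the exposure is available in only four districts. If it is a district characteristic, or is strongly patterned by district, the thousands of births greatly overstate the information on adherence. The usual correction, a cluster-robust variance, needs many more than four clusters. The conceded limit on generalizing concerns who the result applies to. It does not address whether the standard error is right for the four districts studied.

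At stake is a nominally significant link between adherence and deaths that reflects little more than which four districts were sampled. The Discussion relies on the four-district assessment to offset, to a considerable degree, the assumption that retrieved guidance is acted on. A spurious association could therefore be read as support for that step. No primary or secondary treatment comparison depends on it.

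**Working it through.** **Inputs from the article.** Sample size estimation: control neonatal mortality 30/1000, 30% reduction (so 21/1000), ICC ρ = 0.0007256, two-sided 5%, 80% power, 8 clusters per arm, 1065 patients per cluster. Background: national maternal mortality 319 per 100,000 live births. Study site: regional pregnancy-related mortality 594 per 100,000. Table 2: facilities per district.

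**Reproducing the plan's own figure.**
- n = (1.960 + 0.842)² × [0.021×0.979 + 0.030×0.970] / 0.009² = 7.849 × 0.049659 / 0.000081 ≈ 4812 per arm.
- m = n(1−ρ)/(k−nρ) = 4812 × 0.9992744 / (8 − 4812 × 0.0007256) ≈ 1066.5, against the stated 1065.

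The inputs are understood correctly. The article gives no size or power for the adherence analysis.

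**Adherence as one value per district.**
- Design effect = 1 + (1065−1) × 0.0007256 = 1.77.
- Type I error of an ordinary logistic test = 2[1 − Φ(1.96/√1.77)] = 2[1 − Φ(1.472)] ≈ 14.1%.
- With 1650 births per district (an assumption: 1100 a year for 18 months), the design effect is 2.20 and the error is 18.6%.
- A correct district-level slope test has 4 − 2 = 2 df and critical t 4.30. The correlation across the four districts must then reach 4.303/√(4.303² + 2) ≈ 0.95.

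**Simulation under no association.** Each scenario used 2,000 data sets with 4 districts, 1065 births each, mean mortality 0.03 and beta-binomial deaths at the protocol's ICC. District adherence was drawn uniformly from 0.3 to 0.9. In the facility scenario there were ten equal facilities per district, with adherence scattered around the district value (SD 0.15) and no extra mortality variation between facilities in a district. These adherence and facility settings are assumptions.

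| Method | Adherence by district | Adherence by facility |
|---|---|---|
| Ordinary logistic, district ignored | 13.6% | 10.2% |
| Cluster-robust, normal reference | 34.6% | 22.6% |
| Cluster-robust, t with 3 df | 20.5% | 8.9% |
| District-level regression, 2 df | 5.0% | – |
| Logistic with district fixed effects | – | 5.0% |

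With an assumed larger ICC of 0.003, ordinary logistic regression rejects 32.8% of the time by district and 20.1% by facility.

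**Number of events.** Four districts give 4 × 1065 = 4260 births.
- Neonatal deaths: 4260 × 0.021 = 89 to 4260 × 0.030 = 128.
- Maternal deaths: 4260 × 319/100,000 = 13.6 to 4260 × 594/100,000 = 25.3.

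**Could adherence and outcome be matched below district?** From Table 2, the smallest possible pairs hold 6 + 6 (intervention) and 9 + 10 (control) facilities, 31 in all. The largest hold 15 + 11 and 19 + 15, 60 in all. So within-district variation may exist. Table 1 takes neonatal deaths from the facility at non-hospital sites, but takes maternal deaths and total deliveries from DHIMS-2 for every facility type. Data collection says non-hospital sites reach that system only as aggregates through the district directorate. A facility-level denominator is therefore not assured by the text, and no link from a checklist case to its outcome is described.

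**The case against.** The best defence is that the level of the exposure is not stated. The phrase about clusters belongs to the descriptive sentence, while the regression sentence speaks of provider adherence, which a checklist could record by provider, facility or case. The authors know about clustering, as the preceding paragraph shows. A journal article may also leave the details of a sub-study model to a fuller document. Nor does the article mention p-values or confidence intervals in the adherence sentence.

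Much of this stands, and it rules out several stronger readings that a reader might infer:

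- **That no valid interval is possible.** Not supported. A fixed-effects model held 5.0% in the facility scenario, and a 2-df district analysis also held 5.0%.
- **That the model necessarily has four independent units.** Not supported. Between 31 and 60 facilities could contribute.
- **That adjusting for arm and resource level leaves no degrees of freedom.** This is true of four district values, but the adherence sentence names neither covariate.
- **That purposive selection by itself invalidates the intervals.** It limits generalizing, which the article concedes. Confounding of adherence with mortality is a general limit of any such observational association.
- **That the regression is the tool meant to account for the intervention's success or failure.** The article gives that role to the qualitative work.

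The defence does not remove the point. A fuller document can specify a unit, but it cannot add districts. The ordinary and cluster-robust analyses that the sentence most naturally invites were anti-conservative at both levels examined.

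**Conclusion.** The concern holds in limited form. The article commits to a mortality regression on an exposure measured in four purposively selected districts, with no clustering provision attached to it. With a district-level exposure, the error at a nominal 5% is about 14% for ordinary logistic regression and about 20% to 35% for standard cluster-robust inference. With a facility-level exposure and district ignored, it is about 10%. The district-level method that keeps its level has 2 df and almost no power. Maternal mortality, with some 14 to 25 deaths, is too sparse for a useful association estimate at any level.

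The 14% rests on the protocol's ICC and 1065 births per district. The facility figures also rest on ten equal facilities per district and no mortality variation between facilities within a district. That last condition is favourable, because the Study site section says lower-level facilities refer cases to hospitals. For the same reason the 5.0% for fixed effects is a best case, which supports treating such a model as exploratory. The issue is confined to an explanatory sub-study and does not touch the primary analysis.

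**What to change.** Replace the regression sentence by a table that sets adherence beside neonatal and maternal mortality for each of the four districts, at baseline and at the end. Give no p-values or confidence intervals, and label the comparison explanatory.

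If adherence and outcomes can be matched by facility or by case within district, a logistic model with district fixed effects may be added, labelled exploratory only. The unit, the source of its denominator and the handling of extra variation between facilities should then be stated.

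The cost is a sentence or two of analysis text and the loss of an inferential association estimate that four districts cannot support. No data collection changes.

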## Expected outcome

This intervention is expected to improve clinical decision-making which will lead to a decline in maternal and neonatal deaths (Fig. 4). Neonatal and maternal mortality rates based on the number of live births, neonatal deaths, including perinatal deaths, and the number of maternal deaths in each cluster as well as in each arm will be estimated. These rates estimated will be compared to the rates before the intervention.

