## Methods/design

### Study design

A cluster randomized controlled trial (CRCT) to evaluate the effect of a mobile clinical decision-making support system on maternal and neonatal mortality and morbidity will be conducted in 16 districts in the Eastern Region (ER) of Ghana. This study will comprise three components: (1) a baseline study to assess the characteristics of the health facilities and outcome measures of interest in study sites, (2) implementation of a CDMSS for 18 months and (3) a sub-study to assess the QOC of maternal and neonatal care services at baseline and at the end of the study.

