## Monitoring

Uptake of the intervention will be monitored by the frequency of intervention usage using data about requests made to the USSD collected by the telecommunication company providing technical support for the USSD. All health facilities in the intervention arm will be visited periodically to assess the functionality of the intervention on site. Research assistants (in this case, district health information officers have been recruited) will be trained to supervise data collection activities in the non-hospital facilities in all clusters and to provide updates concerning challenges providers may face with the use of the USSD platform to the research team. The supervisory role of the district health information officers includes ensuring that documentation from the non-hospital facilities is complete and collation of completed data collection forms for submission to the project team. The district health information officers will not make any changes to what is recorded on the completed forms. Thus, they will not assess morbidity or mortality causation.

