## Data collection

Data about district and facility characteristics in both arms of the study using a structured questionnaire will be collected. These include human and logistical resources, ANC attendance, number of deliveries, obstetric and neonatal admissions, and primary and secondary outcomes at the baseline and at the end of the study.

The impact of the intervention will be evaluated by extraction of data of outcome measures of interest from the district health information management system-2 (DHIMS-2) database which has been shown to provide reliable estimates of measures [46, 47]. This study will assess the effect of a CDMSS on the commonest causes of neonatal and maternal morbidity and mortality in Ghana. Protocols for diagnosis of these conditions are standardized by the Ghana Health Service across the different categories of health facilities, hence diagnosis across facility type are similar. We assume that health care workers make accurate diagnosis of these common sources of morbidity most of which diagnosis can be made using physical examination and rapid diagnostic tests. The diagnoses made by these health care workers across the different categories of health facilities forms the basis of data entered in the DHIMS-2. Details of all the outcome measures the CRCT seeks to extract from the DHIMS-2; however, covers only hospital data. The non-hospital health facilities report only aggregate data through their district health directorate into the DHIMS-2. Details of outcome measures of interest to the CRCT will, therefore, be collected at the facility level for non-hospital facilities participating in the trial. The diagnosis will be based on what is recorded in the DHIMS-2 or what is recorded in the facility health record books by the health care providers as these diagnoses are expected to follow the standard case definitions for Ghana. Availability of network connectivity in health facilities will be measured during the postintervention evaluation using a Likert scale administered to the health care providers.

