## Statistical analysis

Data analysis and reporting will be in line with the Consolidated Standards of Reporting Trials (CONSORT) Statement guidelines [48]. In this study, randomization was done at the district level and not at the health facility level. All health facilities within a district, therefore, form a cluster. Clusters may differ slightly in their characteristics as can be seen in the larger number of non-hospital health facilities in the control arm (Table 2). We will conduct descriptive analysis of both intervention and reference groups at baseline to explore potential differences in study baseline characteristics of clusters and participants in both study arms. To assess the risk of imbalance in baseline characteristics among the clusters, we will use the c-statistic of the propensity score model of the study. The c-statistic of the propensity score model of the study is considered an appropriate tool to detect baseline imbalance in CRCTs where sample size is large and when a large number of covariates are measured [49]. Any observed imbalance in the baseline characteristics of clusters will be adjusted for in the statistical analysis.

The effect of the CDMSS on primary and secondary outcomes will be analyzed based on the principle of intention-to-treat to minimize over-estimation of the effect of the intervention. Logistic regression will be applied to investigate the effect of CDMSS on all outcome measures considering a potential clustering effect of the CRCT design and adjusting for potential confounders. Results will be reported as relative risks with corresponding 95% confidence intervals. A two-tailed statistical significant level of 0.05 will be used. Among clusters in the intervention arm, descriptive analysis of the availability of network connectivity in health facilities will be done and any significant difference in network availability will be adjusted for using logistic regression. STATA software package [50] and MLwiN software version 2.1 [51] will be employed to handle the analysis.

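### Baseline outcomes are collected in both arms, but their only stated use is a before-after comparison, and covariate adjustment is left to observed imbalance or unnamed confounders; baseline mortality should be a fixed covariate

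*Protocol article*

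**What the plan says.** Study design lists as its first component "a baseline study to assess the characteristics of the health facilities and outcome measures of interest in study sites". Data collection states that "Data about district and facility characteristics in both arms of the study using a structured questionnaire will be collected" and includes "primary and secondary outcomes at the baseline and at the end of the study". Baseline mortality should therefore be available for all 16 districts.

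Two sections bear on how it is used.

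- **Expected outcome.** Neonatal and maternal mortality rates "in each cluster as well as in each arm will be estimated", and then "These rates estimated will be compared to the rates before the intervention". The section does not say that the changes will be compared between arms, and it does not say that they will be tested.
- **Statistical analysis.** The effect is estimated by intention-to-treat logistic regression, "considering a potential clustering effect of the CRCT design and adjusting for potential confounders". A separate rule governs baseline differences: "Any observed imbalance in the baseline characteristics of clusters will be adjusted for in the statistical analysis". Imbalance is to be assessed with the c-statistic of a propensity score model. Baseline mortality is neither named as a covariate nor excluded.

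Monitoring adds that, during the trial, district information officers supervise non-hospital data collection in all clusters, which includes "ensuring that documentation from the non-hospital facilities is complete".

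**The concern.** Two things are fixed badly.

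First, the change from before to after within an arm is not protected by randomisation. It combines any intervention effect with secular trend, with other maternal and newborn programmes (the Discussion accepts that these could influence results) and with any change in how completely deaths are recorded. Expected outcome opens by predicting a decline in deaths. A fall in the intervention arm could therefore be read as confirmation even if the between-arm result is null.

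Second, the adjustment rule depends on the data. A prognostic covariate is worth including because it predicts the outcome, whether or not it happens to differ between arms. Under the stated rule, whether the district's own earlier mortality enters the primary model is settled only after the baseline data have been examined. The c-statistic does not settle it either, because it is one overall figure and does not say which covariate to adjust for. With 16 randomised units, chance imbalance is likely and the choice of covariates can move the estimate.

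**Working it through.** **1. The plan's own figure.** Inputs from Sample size estimation: p0 = 0.030, a 30% reduction so p1 = 0.021, ICC ρ = 0.0007256, k = 8 clusters per arm, two-sided 0.05, power 80%.

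- n = θ[p1(1-p1) + p0(1-p0)]/(p1-p0)² = 7.849 × (0.020559 + 0.0291)/0.009² = 4812 per arm.
- m = n(1-ρ)/(k-nρ) = 1066.5 per cluster. With θ rounded to 7.84 it is 1064.4. The stated 1065 reproduces.

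**2. Unadjusted power.** Design effect = 1 + 1064 × 0.0007256 = 1.772. SE = √[0.049659/(8 × 1065) × 1.772] = 0.00321, and 0.009/0.00321 = 2.80. Power is 80% on the normal approximation and 74% on the t distribution with 14 df.

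**3. Effect of adjusting for the baseline district rate.** Two inputs are assumptions:

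- baseline births per cluster: 710, which is 1065 × 12/18, a 12-month baseline against an 18-month trial;
- correlation of true district effects between periods: c = 0.6 to 0.9.

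The between-cluster share of the variance of a cluster rate is s = mρ/[1 + (m-1)ρ]. At the stated ICC this is 0.340 at baseline and 0.436 in the trial period. The correlation of the observed rates is r = c√(s0·s1), which is 0.231 to 0.347.

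The variance is multiplied by (1-r²) × [1 + 1/(2k-4)]. The second factor, 13/12 at k = 8, is the expected cost of estimating the slope when arm baselines differ by chance. Leaving it out overstates the gain. Adjusted power uses 13 df. I simulated cluster-level ANCOVA, 200,000 trials per cell; variance ratios agree with the formula to within 0.004.

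| ICC | 1-r² (c = 0.6; 0.9) | × 13/12 | Variance change | Power, unadjusted | Power, adjusted |
|---|---|---|---|---|---|
| 0.0007256 (stated) | 0.947; 0.880 | 1.025; 0.953 | +3% to -5% | 74% | 73-76% |
| 0.0015 (assumed) | 0.886; 0.743 | 0.959; 0.805 | about -4% to -19% | 58% | 59-67% |
| 0.003 (assumed) | 0.813; 0.579 | 0.881; 0.628 | -12% to -37% | 40% | 44-57% |

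Sensitivity at the stated ICC: if the baseline period were as large as the trial period and c ran from 0.5 to 1.0, r² would be 0.048 to 0.190, and the factor 0.952 × 13/12 = 1.03 to 0.810 × 13/12 = 0.88.

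**4. Recording.** For non-hospital facilities, Table 1 takes neonatal deaths from facility records, the documentation the officers supervise during the trial. Summing health centres, CHPS and maternity homes in Table 2 gives 61 non-hospital facilities in the intervention arm and 88 in control. If supervision makes records more complete than they were at baseline, counted deaths rise in both arms, possibly by different amounts. The protocol does not quantify this.

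**The case against.** The strongest reply is that the protocol already has the right primary analysis. Statistical analysis specifies a between-arm, intention-to-treat regression that allows for clustering. The before-after sentence stands in another section, names no test and covers both arms, so the control-arm change would be visible alongside. This stands. A reader might infer that the before-after comparison replaces the randomised contrast; the text does not support that.

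A reader might also infer that baseline mortality can enter the model only if it is flagged as imbalanced. That goes too far as well, because the general provision for confounders carries no such condition. A full covariate list may properly sit in an analysis plan that is not shown, and its absence here is no fault. What remains is the rule that is stated: adjustment for baseline characteristics triggered by observed imbalance.

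On precision, a reader might infer that omitting baseline mortality wastes substantial information. At the stated ICC it does not, once the slope is paid for. At a correlation of 0.6, adjustment costs about one point of power.

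On recording, the officers work in all clusters, and the 61 v 88 difference could affect the trial-period contrast too, so the problem is not peculiar to the before-after comparison. Changed recording would also make baseline a weaker predictor. The Study site section reports regional neonatal mortality of 29 and 30 per 1000 with little change, so no large trend is documented. These points limit the size of the concern; they do not make a within-arm change a valid estimate of effect.

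Finally, 2014 is called the baseline year when district selection is explained. That the baseline outcomes are also for 2014 is an inference.

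**Conclusion.** The point holds as one of pre-specification. The protocol should fix baseline mortality as a covariate, whatever imbalance is seen, and should keep the before-after comparison out of the inference about effect.

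Precision is a secondary argument. At the protocol's own ICC the gain is roughly nil: variance +3% to -5%, power 74% to 73-76%. It becomes worthwhile only if the ICC is well above the single value cited: variance falls about 4-19% at 0.0015 and 12-37% at 0.003. All of this rests on the assumed 710 baseline births and correlation of 0.6 to 0.9, neither of which the protocol gives. The firmer benefits are a primary model settled in advance, protection against chance baseline imbalance among 16 districts, and some insurance against a higher ICC. None of this invalidates the planned between-arm analysis.

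**What to change.** 1. Replace the before-after sentence under Expected outcome with wording such as: *The effect of the intervention is the between-arm comparison of trial-period rates, adjusted for each district's baseline rate of the same outcome.*
2. Under Statistical analysis, state that this adjustment is made whatever imbalance is observed. Apply it to neonatal mortality at least, and to each secondary outcome whose baseline rate is available on the same definition and from the same type of source. State the baseline period for the outcomes.
3. Report changes from baseline by cluster and arm descriptively, without tests. If change is to be compared formally, compare it between arms.

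The cost is wording, one degree of freedom, and a possible loss of about one point of power if the ICC is as low as stated. Baseline outcomes are already to be collected. The one practical check is whether non-hospital baseline records match the trial-period definitions.
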